**Methods:**

The proposed research is a single-site, mixed methods, single-arm cohort study evaluating MBC. Eligible participants will have chronic breathlessness as defined by a modified Medical Research Council score of at least 2 and COPD confirmed by spirometry. Initially, participants will undergo a holistic medical assessment to understand factors contributing to breathlessness and to optimize therapy. The MBC intervention will be a 9-week, home-based, multidisciplinary program (with contributions from medical, nursing, physiotherapy, and occupational therapy clinicians). Central to this program will be coaching for breathlessness self-management using individualized, multicomponent strategies. Breathlessness impact will be assessed using questionnaire instruments measuring breathlessness mastery, symptom burden, quality of life, and psychological distress, with the Chronic Respiratory Questionnaire’s mastery subscale as primary outcome. Assessments will be undertaken at baseline, 9 weeks, and 52 weeks; 12-month exacerbation rates, health care use, and rescue medication use will be monitored and measured against participants’ historical data. Participant and carer experiences will be evaluated using qualitative methods to inform development of the service.

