**Exclusion criteria**
Bed-bound or moribundCognitive impairment that precludes ability to engage and participate in education strategiesCurrent active diagnosis of cancer, substance abuse (other than nicotine dependence), or other uncontrolled medical or psychiatric disorderModerate or severe exacerbation of COPD (defined as an escalation of treatment to include systemic corticosteroids and/or antibiotics [10]) within 4 weeksInsufficient command of the English language to comprehend and engage with interventionsCurrent enrollment in pulmonary rehabilitation program (may participate if still eligible upon program completion or if involved in a long-term maintenance program)

Description of Intervention: MBC

The proposed intervention, the MBC, is a 9-week program to manage chronic refractory breathlessness. The MBC team will include a respiratory physician, occupational therapist, specialist respiratory nurse, and physiotherapist with referrals as needed for dietetic and speech pathology services. The MBC itself will comprise 9 health care interactions of 60 to 90 minutes, with most visits occurring within the patient’s home as outlined in Table 1.

**Table 1 table1:** Macarthur Breathless Clinic 9-week program.

Schedule	Location	Activity
Week 1	Patient’s home	Initial assessment, respiratory nurse
Week 2	Outpatient clinic	Medical assessment by respiratory physician Multidisciplinary team assessment of breathlessness, contributing factors and impacts to develop recommendations and management plan Introduction to nonpharmacologic strategies, including provision and use of a battery-operated handheld fan Fact sheets on managing breathlessness
Week 3	Patient’s home	Physiotherapist
Week 4	Patient’s home	Occupational therapist
Week 5	Patient’s home	Respiratory nurse
Week 6	Patient’s home	Physiotherapist
Week 7	Patient’s home	Respiratory nurse
Week 8	Patient’s home	Final assessments, research assistant
Week 9	Outpatient clinic	Closure and follow-up arrangements, multidisciplinary team

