An initial holistic medical assessment will be performed by an experienced multidisciplinary team, including a respiratory physician, specialist respiratory nurse, and respiratory physiotherapist. The holistic assessment framework that will be used for breathlessness is systematic and encompasses the skill set of the multidisciplinary team ensuring the whole person is considered. The assessment template in Multimedia Appendix 2 outlines the domains considered. The assessment recognizes the multifactorial nature of breathlessness, with possible contributions from many interconnected parts, including medical history, comorbid diseases, medications, mental and social factors, understanding and beliefs about breathlessness, self-management strategies, inhaler technique, current functional capacity, exercise history, and even incontinence.

Following initial assessment and optimization of medications, nonpharmacological therapies will commence. Through the MBC, patients and carers will receive education about breathlessness management and daily coping strategies to enhance independence and productivity. The clinical team will coach participants through individualized strategies to improve management of breathlessness in daily activities (Table 2) based on Cambridge Breathlessness Intervention Service’s “breathing, thinking, functioning” clinical model [11]. A broad repertoire of standard interventions will be tailored to individual patients’ needs, goals, and preferences.

**Table 2 table2:** Nonpharmacologic breathlessness interventions.

Theme	Examples
Beliefs	Validation of breathlessness Clarifying mistaken beliefs—for example, breathlessness is not always due to low oxygen levels and breathlessness itself is not dangerous Motivational interviewing
Strategies	Use of a handheld battery-operated fan Breathing techniques such as “breathing around a rectangle,” “pursed lip breathing,” “flickering the candle,” “paced breathing,” or “diaphragmatic breathing” explained with an accompanying fact sheet Positions to relieve breathlessness Sputum clearance techniques
Exercise	Walking program with use of a pedometer Strengthening exercises
Aids/efficiency	Shower chair 4-wheel walker Energy conservation Home modifications Referral to dietitian if underweight or malnourished

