Education and self-management	Inhaler technique Disease education (including medications and other therapies) Written breathlessness action plans Written chronic obstructive pulmonary disease exacerbation action plan Breathlessness DVD to reinforce key interventions Relaxation CD Fact sheets on managing breathlessness
Miscellaneous	Carer support Assessment and management of incontinence

The role of each clinician and coaching topics covered is illustrated in Figure 2, noting that any cross-over of topics between clinicians will serve as reinforcement of strategies provided or will allow colleague cross-cover.

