#### Health Care Resource Use Outcomes

Self-reported exacerbation, emergency department (ED) visit, and hospitalization data will be collected. South Western Sydney Local Health District’s electronic medical records will also be systematically reviewed to verify participant self-reports. Data will be updated at 6 and 12 months from MBC enrollment and will include the annual number of the following:

ED presentations (all presentations), lasting <24 hours, that do not result in hospitalization, as well as breathlessness-related ED presentations, lasting <24 hours, that do not result in hospitalizationUnplanned hospitalizations, including unplanned hospitalizations due to breathlessnessHospital length of stay in bed days (all unplanned hospitalizations), as well as breathlessness-related hospital bed daysExacerbations of COPD counted by patient-reported activation of COPD action plan, along with occasions of prescription of antibiotics and/or corticosteroid for the treatment of symptoms of respiratory exacerbation during hospitalized events

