#### Statistical Analysis Plan

Descriptive statistics will be applied to the study population to characterize them in terms of demographic and baseline clinical parameters. Normally distributed continuous variables will be expressed as mean (SD), nonparametric variables will be defined by median and range, while categorical variables will be expressed as percentages.

Breathlessness outcomes will be compared across 3 time points: baseline, 9 weeks, and 52 weeks using repeated measures ANOVA. Predictors of response will be sought using linear regression models with sex, forced expiratory volume (FEV) in 1 second, ratio of FEV to forced vital capacity, BMI, Montreal Cognitive Assessment, and baseline anxiety and depression scores as prespecified variables. Health care use measures and exacerbation data for the 12 months prior to MBC enrollment will be compared with the corresponding values for the 12 months after MBC enrollment, using Student 2-tailed *t* tests or nonparametric tests as appropriate. Protocol completer and dropout populations will be compared in terms of baseline characteristics (sex, age, FEV in 1 second, pack years, BMI, CRQ-Mastery subscale, CAT score, and Montreal Cognitive Assessment) to investigate potential selection bias.

Finally, comparison will be made with patients’ baseline data from the year prior to enrollment in the breathless clinic, benchmarked against nonparticipant comparator hospital deidentified patient medical records with (1) ED presentations for reasons of breathlessness, triaged as “shortness of breath—respiratory” or (2) hospitalized with exacerbations of COPD or heart failure as per diagnostic related group assignment. These benchmarking comparisons will use deidentified electronic medical records and will contribute to exploratory analyses undertaken to better understand the health care use of our sample cohort in the context of the overall health care use patterns of our local population “breathless” groups.

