Our study protocol excludes patients based on English language proficiency, which represents another important limitation. Ideally language should not prevent equitable access to medical care nor opportunities to participate in health research. The decision to include only English-speaking participants was made due to significant ethnic and cultural differences in the expression and description of breathlessness. Additionally, some of the outcome measures are only validated in English. The exclusion of people who do not speak English will limit the generalizability of our results to the English-speaking population. The authors estimate the impact of exclusion due to English proficiency to be small as shown in Figure 1, noting that exclusion percentages are estimates based on census data. The 2021 census data from the Australian Bureau of Statistics inform that the Macarthur and Wollondilly local government areas have, when compared with Sydney and New South Wales, a higher concentration of English-only speakers [22]. To mitigate the impact on generalizability and perhaps to provide an alternative means to characterize and express the severity of breathlessness in future iterations of the program, the Dalhousie pictorial scales, which help bypass literacy and language barriers, have been included as an outcome measure.

Finally, regarding COPD exacerbations, the authors recognize that patient recall of these events is notoriously poor, particularly for milder events, either self-treated or treated via primary care in the community. Moreover, Australia’s national guidelines, COPD-X, recommend that such patients have an exacerbation plan, along with prescriptions for relevant rescue medications making it even more complicated to establish the timing of these events. We will seek to confirm more severe events, resulting in an ED visit or hospitalization, systematically using local hospital electronic medical records. However, patient reports of exacerbation and health care use events will be sought nonetheless, given the possibility of capturing additional events occurring outside our health district, interstate, or within primary care, while acknowledging that the reporting and therefore capture of these events will be less reliable.

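### The community-treated part of the exacerbation count depends on an action plan that the clinic itself supplies, so the before/after comparison of this secondary outcome leans toward an apparent increase.

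*Protocol article*

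**What the plan says.** Four places in the protocol article bear on this point.

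- **Counting rule** (Health Care Resource Use Outcomes). Exacerbations are "counted by patient-reported activation of COPD action plan, along with occasions of prescription of antibiotics and/or corticosteroid for the treatment of symptoms". The sentence then restricts the prescriptions to those given "for the treatment of symptoms of respiratory exacerbation during hospitalized events". An event treated outside hospital therefore enters the count through plan activation.
- **Intervention content** (Table 2, education and self-management). The listed materials include "Written chronic obstructive pulmonary disease exacerbation action plan". The text introducing Table 2 adds a qualification: "A broad repertoire of standard interventions will be tailored to individual patients’ needs, goals, and preferences".
- **Comparison** (Statistical Analysis Plan). "Health care use measures and exacerbation data for the 12 months prior to MBC enrollment will be compared with the corresponding values". The later period is the year following enrollment, and the comparison is by t test or a nonparametric test. Under Study Design, participants are their own controls.
- **Another definition in the same article** (Textbox 1, exclusion criteria). A moderate or severe exacerbation is "defined as an escalation of treatment to include systemic corticosteroids and/or antibiotics", with no reference to a plan.

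Strengths and Limitations concedes that "patient recall of these events is notoriously poor, particularly for milder events", and that timing is hard to establish when patients hold plans and rescue prescriptions. It also notes that national guidelines recommend such plans. It does not mention that the clinic hands out the instrument by which community events are counted.

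**The concern.** A before/after comparison without a control group needs the outcome to be ascertained in the same way in both periods. Here one component of the count requires the patient to hold and activate a plan, and the intervention may be what first provides it. For those participants the chance that a community-treated event is counted changes at enrollment, whatever happens to their disease. No parallel group experiences the same change, so the analysis cannot separate a change in disease from a change in counting.

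Exacerbations are named first in the stated secondary aim, and reduced COPD-related health care use is part of the hypothesis. A real reduction could be reported as no change, or even as an increase.

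**Working it through.** The article gives no exacerbation rate, effect size or share of patients with a plan, so there is no figure to reproduce. What follows is an illustration with assumed inputs.

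**Inputs, all assumed**
- h: share of exacerbations treated in hospital, counted alike in both periods.
- q0 and q1: shares of participants holding a plan before and after enrollment.
- Every community event in a plan holder is counted, and none in a participant without a plan.
- Event rates do not depend on plan possession.

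**Formula.** With no true change, the counted ratio after/before is

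[h + (1 − h)·q1] / [h + (1 − h)·q0].

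A true rate ratio r that applies equally to hospital and community events multiplies this by r.

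**No true change, q1 = 1** (the numerator is then 1)

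| h | q0 = 0.25 | q0 = 0.50 | q0 = 0.75 | q0 = 1.00 |
|---|---|---|---|---|
| 0.1 | 3.08 | 1.82 | 1.29 | 1.00 |
| 0.2 | 2.50 | 1.67 | 1.25 | 1.00 |
| 0.5 | 1.60 | 1.33 | 1.14 | 1.00 |

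Example: h = 0.2 and q0 = 0.50 give 1 / (0.2 + 0.8 × 0.50) = 1 / 0.60 = 1.67.

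**True 25% reduction, h = 0.2, q1 = 1**
- q0 = 0.25: 0.75 / 0.40 = 1.88
- q0 = 0.50: 0.75 / 0.60 = 1.25
- q0 = 0.75: 0.75 / 0.80 = 0.94
- q0 = 1.00: 0.75

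The reduction is reversed if half held a plan before, and mostly hidden if three quarters did.

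**Not everyone receives a plan: q1 = 0.8, h = 0.2, no true change.** The numerator is 0.2 + 0.8 × 0.8 = 0.84.
- q0 = 0.25: 0.84 / 0.40 = 2.10
- q0 = 0.50: 0.84 / 0.60 = 1.40
- q0 = 0.75: 0.84 / 0.80 = 1.05

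The distortion is zero only when q0 = q1. If community events are counted in both periods by a rule that does not depend on a plan, q drops out and the no-change ratio is 1.00 for any plan possession. Differences in recall would remain.

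**The case against.** The strongest reply is that the problem is narrow, partial and in a safe direction.

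- **Narrow.** Treatment courses during hospitalized events do not depend on a plan. Neither do ED presentations, unplanned hospitalizations or bed days, and local electronic records are used to verify these. The primary outcome, CRQ mastery, is not involved. This stands. A reader might infer that exacerbations as a whole, or all health care use, cannot be compared before and after; the document does not support that.
- **Partial.** Guidelines recommend plans, and referrals come from outpatient services or follow COPD-related admissions, so some participants will already hold one. Table 2 items are tailored, and nothing says that every participant gets a plan. This stands and limits the size. It removes the bias only if possession is equal in both periods, which nothing in the article ensures: holding a plan is not an eligibility criterion and no proportion is given.
- **Broader collection than counting.** Self-reported exacerbations are collected by structured interview, and patient reports are sought for events in primary care. A reader might infer that anyone without a plan necessarily scores zero community events in the earlier year. That follows only from the strictest reading of the rule; the interviews may hold more. This helps the remedy, but the stated rule still counts by plan activation and offers no alternative for the earlier year.
- **Direction.** The bias works against the study hypothesis, so by itself it would not create a false claim of benefit. This is true, but a missed or reversed benefit is also a wrong answer.
- **Acknowledged limits.** Poor recall is disclosed; the change of counting instrument is not.

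Two further inferences should not be added. The article times only the 6- and 12-month updates, so a full year's recall at enrollment is not documented. The abstract says that "12-month exacerbation rates, health care use, and rescue medication use will be monitored and measured against" historical data, but how rescue medication is measured may be set out in the full protocol.

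**Conclusion.** The point holds for the community-treated part of one secondary outcome. As written, the counting instrument can change at enrollment for participants who first receive a plan through the clinic. The effect is toward more counted exacerbations afterwards.

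The size is unknown because the share already holding a plan is unknown. With 20% of events hospital-treated and all participants holding a plan afterwards, the no-change ratio runs from 1.67 (half held a plan before) through 1.25 (three quarters) to 1.00 (all). With half of events hospital-treated and three quarters already holding a plan, it is only 1.14. None of these inputs comes from the document, so no single figure, such as a doubling of the recorded rate, should be presented as the expected distortion.

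The matter is worth correcting because the rule is stated rather than left open, the article already contains a definition that does not depend on a plan, and analysis is reported as ongoing.

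**What to change.** Before the analysis is completed:

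1. Make exacerbations verified in hospital and ED electronic records the main before/after exacerbation comparison. The article already plans to confirm these events systematically.
2. Where interview and record data allow, count community events in both years by one treatment-based definition that does not require a plan, such as the one already used in Textbox 1. State how many events cannot be classified in each year.
3. Report action-plan activation descriptively, for the period after enrollment only.
4. If plan possession before enrollment can be recovered from existing assessment records, show the comparison separately by it. It can no longer be newly recorded at entry, because participants have completed the protocol.
5. State in the limitations that the intervention supplies the plan used for counting.

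The cost is some reclassification of data already collected and fewer events, hence less precision, in the main exacerbation comparison. If the interviews did not capture community courses taken without a plan, step 2 will be incomplete, but steps 1, 3 and 5 remain possible. The change removes only the shift in counting; the other limits of an uncontrolled comparison, including recall, remain.

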#### Statistical Analysis Plan

Descriptive statistics will be applied to the study population to characterize them in terms of demographic and baseline clinical parameters. Normally distributed continuous variables will be expressed as mean (SD), nonparametric variables will be defined by median and range, while categorical variables will be expressed as percentages.

Breathlessness outcomes will be compared across 3 time points: baseline, 9 weeks, and 52 weeks using repeated measures ANOVA. Predictors of response will be sought using linear regression models with sex, forced expiratory volume (FEV) in 1 second, ratio of FEV to forced vital capacity, BMI, Montreal Cognitive Assessment, and baseline anxiety and depression scores as prespecified variables. Health care use measures and exacerbation data for the 12 months prior to MBC enrollment will be compared with the corresponding values for the 12 months after MBC enrollment, using Student 2-tailed *t* tests or nonparametric tests as appropriate. Protocol completer and dropout populations will be compared in terms of baseline characteristics (sex, age, FEV in 1 second, pack years, BMI, CRQ-Mastery subscale, CAT score, and Montreal Cognitive Assessment) to investigate potential selection bias.

Finally, comparison will be made with patients’ baseline data from the year prior to enrollment in the breathless clinic, benchmarked against nonparticipant comparator hospital deidentified patient medical records with (1) ED presentations for reasons of breathlessness, triaged as “shortness of breath—respiratory” or (2) hospitalized with exacerbations of COPD or heart failure as per diagnostic related group assignment. These benchmarking comparisons will use deidentified electronic medical records and will contribute to exploratory analyses undertaken to better understand the health care use of our sample cohort in the context of the overall health care use patterns of our local population “breathless” groups.

